**Chart 1: The NEWS scoring system**

| Physiological parameter        | 3           | 2      | 1         | Score 0                   | 1               | 2               | 3                   |
|--------------------------------|-------------|--------|-----------|---------------------------|-----------------|-----------------|---------------------|
| Respiration rate (per minute)  | $\leq 8$    |        | 9–11      | 12–20                     |                 | 21–24           | $\geq 25$           |
| SpO 2 Scale 1 (%)   | $\leq 91$   | 92–93  | 94–95     | $\geq 96$                 |                 |                 |                     |
| SpO 2 Scale 2 (%)   | $\leq 83$   | 84–85  | 86–87     | 88–92
$\geq 93$ on air | 93–94 on oxygen | 95–96 on oxygen | $\geq 97$ on oxygen |
| Air or oxygen?                 |             | Oxygen |           | Air                       |                 |                 |                     |
| Systolic blood pressure (mmHg) | $\leq 90$   | 91–100 | 101–110   | 111–219                   |                 |                 | $\geq 220$          |
| Pulse (per minute)             | $\leq 40$   |        | 41–50     | 51–90                     | 91–110          | 111–130         | $\geq 131$          |
| Consciousness                  |             |        |           | Alert                     |                 |                 | CVPU                |
| Temperature (°C)               | $\leq 35.0$ |        | 35.1–36.0 | 36.1–38.0                 | 38.1–39.0       | $\geq 39.1$     |                     |

For non-hospitalized patients, measurements will be auto-performed by the patient either assessed by a caregiver or a family member. Training on how to use the provided devices will be performed by USCAR unit at T1, written instructions will be also provided, and additional help will be given

[figure not shown]

upon request by phone or videocall. Measurements will be recorded on the clinical diary that will be provided (Appendix 5). Patients will be contacted daily by USCAR dedicated unit and will communicate by phone their health status that will be registered on a dedicated clinical records form (Appendix 5). USCAR unit approaching COVID-19 patients will use personal protective equipment including a FFP3 (or FFP2) mask, gloves, gown and goggles. FFP3 will be used always in case of any procedure on respiratory tract (including nasopharyngeal swab).

Hospitalized patients can be discharged from the hospital considering the ongoing national and regional recommendations to discharge COVID-19 patient at home. The USCAR unit will then responsible of continuing follow up of the patient according to the timeline described in Appendix 2.

#### 8.4 Other therapies allowed

Patients will not receive any other antiviral treatment, unless considered needed by the physician. All other treatments including anti-hypertensive drugs, medications for diabetes (insulin and oral drugs), antibiotics, hormone therapy can be provided to patients of both groups according to medical judgments. Patients should not receive nonsteroidal anti-inflammatory drugs apart from paracetamol if needed.

Any previous and concomitant medication will be recorded along with:

- Reason for use
- Dates of administration including start and end dates
- Dosage information including dose and frequency

#### 8.5 Safety monitoring and individual stopping rules

Any sign or symptom associated to drug adverse events will be daily reported.

Progressing patients which are in need of oxygen support will be maintained in the trial for follow up purposes, but treatment will be discontinued (Appendix 1). Progressing patients will receive standard of care or additional treatment at the physician discretion.

Another stopping rule includes drug related adverse events grade  $\geq 3$  according to Common Terminology Criteria for Adverse Events (CTCAE) version 5.0.

[figure not shown]

For progressing patients, we will record the admission to the intensive care unit, days in ICU, and the disease outcome (either survivor or non-survivors) by using the Regional surveillance systems. Patients are free to withdraw from participation in the study at any time upon request, without any consequence. Patients should be listed as having withdrawn consent only when they no longer wish to participate in the study and no longer authorize the Investigators to make efforts to continue to obtain their outcome data. Every effort should be made to encourage patients to remain in the study for the duration of their planned outcome assessments. Patients should be educated on the continued scientific importance of their data, even if they discontinue the study. In the case of a patients becoming lost to follow-up, attempts to contact the patient should be made and documented in the patient's medical records.

## 9. Methods

### 9.1 Randomization

Sixty patients will be randomized 2:1 to receive IFN- $\beta$ 1a or control arm. Eligible patients will be randomised (no later than 36 h after enrolment) by means of a computerized central randomization system. All patients will receive a unique patient identification number at enrolling visit when signing the informed consent and before any study procedures are performed. This number must remain constant throughout the entire study.

ISS will prepare a randomization list by using a validated software and the list will be managed by the CRO. The randomization of patients will be closed when 60 patients have been randomized. The randomization will be stratified by sex; for each stratum a sequence of treatments randomly permuted in blocks of variable length (3 or 6) will be generated.

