### **Administrative support:**

**[name], [name] and [name]**

Institute of Translational Pharmacology (IFT)

National Research Council (CNR)

e-mail: [[contact]](mailto:[contact]), [[contact]](mailto:[contact]), [[contact]](mailto:[contact])

Administrative clinical research support on inter-institutional agreements, material transfer agreements, institutional tenders.

.....  
This is an investigator-initiated study. The Steering Committee will take responsibility for study design and data analysis and will operate actions necessary to guarantee that the trial is conducted in accordance with procedures described in this document and good clinical practice. The study is partially funded by Merck. Merck has no role in study design, data collection, management, analysis, data interpretation, manuscript writing, or in the decision to submit manuscripts for publication.

The Steering committee will include at least one representative from all units participating to the study and will be chaired by the Scientific Coordinator of the study ([name]) with the cooperation of a coordination team ([name], [name], [name], [name], [name], [name]). The Steering committee will oversee all the aspects of the project's life: decision about safety, decision for stopping rule, diagnostics issues, capacity development, financial, schedule, partnership, dissemination and exploitation. The Steering committee will hold at least one meeting a week on teleconference. In addition, extraordinary sessions will be held in case of critical issues.

[figure not shown]

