### 9.2 Blinding

This is an open-label study. After the randomization, patient will be notified whether will receive or not the experimental drug.

[figure not shown]

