### 13.2.3 Audits and inspections

The Principal Investigator and the SC will provide all the necessary information and material to the participating centers in order to standardize all the protocol-related procedures and to avoid unexpected variability. Printed and electronic informative material (complete original protocol, informed consent modules, informative modules for patients and relatives, recruitment checklist, graphic timeline of interventions and visits, order list for physicians and nurses) will be distributed to Spallanzani Hospital and USCAR. Source data/documents must be available to inspections by the designee or Health Authorities.

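### Section 9.1 discloses the block lengths to the staff who enrol in an open-label trial, so some allocations can be deduced in advance

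*Protocol*

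**What the plan says.** Protocol, Section 9.1 gives the whole allocation scheme.

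- Size and ratio: "Sixty patients will be randomized 2:1 to receive" IFN-β1a or control.
- Strata: "The randomization will be stratified by sex". Enrolling unit is not a factor, so both units draw on the same two lists.
- Blocks: "for each stratum a sequence of treatments randomly permuted in blocks of variable length (3 or 6) will be generated". At 2:1, a block of 3 holds 2 IFN and 1 control, and a block of 6 holds 4 IFN and 2 controls.
- Concealment: patients are randomised "by means of a computerized central randomization system", from a list prepared by ISS and managed by the CRO, "no later than 36 h after enrolment".

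Section 9.2 makes the trial open-label: "After the randomization, patient will be notified whether will receive or not the experimental drug". Section 7.3 names USCAR (home and residential care) and Spallanzani Hospital as the units that assess and enrol. Section 13.2.3 distributes to both of them material that includes the "complete original protocol, informed consent modules, informative modules for patients and relatives, recruitment checklist". Nowhere does the protocol withhold the block lengths from enrolling staff.

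**The concern.** A central system hides the list. It does not stop someone who knows the possible block lengths and the past allocations from deducing what must come next. Here the lengths are in a document that the enrolling staff receive, and the open label reveals each past allocation to those who treat the patient.

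The entry decision leaves room to use such knowledge. Staff choose whom to approach, and Section 7.2.2 lets the investigator exclude a patient on suspicion of poor compliance. A frailer or milder patient could be approached or passed over according to the arm expected next. With 20 controls planned, one patient is 1/20 = 5 percentage points of that arm's event rate. Section 5.1.1 also counts any other clear clinical sign of worsening as progression, judged without masking, so concealment is one of the few protections against bias that this design has.

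**Working it through.** **The plan's own figures.** The protocol gives no figure for predictability. Its sample size matters here only because it fixes the number of controls, and it reproduces. With p = 0.50 (control) and 0.15 (IFN), ratio 2, two-sided 5% and 80% power, the mean proportion is (0.50 + 2 × 0.15)/3 = 0.267. Then

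n(control) = [1.96 √(3 × 0.267 × 0.733) + 0.842 √(2 × 0.25 + 0.1275)]² / (2 × 0.35²) = 19.2,

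which rounds up to 20 controls and 40 IFN, as in Section 5.4.

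**Inputs for predictability.** From Sections 9.1 and 9.2: lengths 3 and 6, ratio 2:1, two strata, past allocations unmasked. Assumed, because the protocol does not say: each length has probability 1/2 (varied from 1/3 to 2/3), strata of 30 and 30 (checked at 40 and 20), and the share of a stratum's allocations that a unit sees.

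**By hand, at the start of a stratum** (I = IFN, C = control):

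- After C: both lengths remain equally likely. P(next is I) = ½ × 1 + ½ × 4/5 = 0.90.
- After I, I: likelihood 1/3 under a block of 3 and 4/6 × 3/5 = 2/5 under a block of 6, so P(block of 3) = (1/3)/(1/3 + 2/5) = 5/11. P(next is C) = 5/11 × 1 + 6/11 × 1/2 = 0.73, against 0.33 by default.
- After C, C: a block of 3 is impossible, so the next four are certainly IFN. This start has probability ½ × 2/6 × 1/5 = 1/30.
- After I, I, I, I: again only a block of 6 fits, and the next two are certainly control. Probability ½ × 1/15 = 1/30.

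**Over the whole list.** Later on, block boundaries must be inferred. A Bayesian filter over the position within the block was therefore run on simulated lists (4,000 trials per scenario), giving the probability of each arm at each entry. As a check, fixed blocks of 3 can be done by hand. The starts C, IC and II each have probability 1/3 and leave 2, 1 and 1 certain entries, so (2 + 1 + 1)/3 ÷ 3 = 44.4%, which is what the simulation returns.

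| Lengths | Share of stratum seen | Next arm certain | Certain control | Best guess right |
|---|---|---|---|---|
| Reference: always guess IFN | – | 0% | 0% | 66.7% |
| 3 or 6 | all | 9.9% | 2.1% | 75.4% |
| 3 or 6 | 75% | 4.1% | 0.4% | 70.3% |
| 3 or 6 | 50% | 1.3% | 0.1% | 68.0% |
| 3 or 6 | 25% | 0.2% | 0.0% | 66.9% |
| 3 only (fixed) | all | 44.4% | 11.1% | 77.8% |
| 6 only (fixed) | all | 28.9% | 6.7% | 74.5% |

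Repeat runs gave 9.4% to 10.0% certain at full sight, 3.9% to 4.1% at 75% (guesses right 70% to 71%), and 1.3% to 1.4% at half. At full sight, 0.099 × 60 = 5.9 patients are certain and 0.021 × 60 = 1.3 are certain controls. Varying the share of 3-blocks from 2/3 to 1/3 moves certainty from 7.2% to 11.9%; strata of 40 and 20 give 9.7%.

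**Which row applies.** Section 14 budgets home oximeters, sphygmomanometers and home care for 30 of 60 patients, so an even split between units is the natural planning case, and that is the half-sight row. Section 12 says that the epidemic will affect the proportion enrolled in each setting, so one unit could see much more.

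**The case against.** The scheme is conventional and has real safeguards: central randomisation, a list kept away from the sites, and two block lengths instead of one. Mixing 3 and 6 brings certainty at full sight down from 44.4% or 28.9% to about 10%. The lists are shared between units, so neither unit normally sees a full sequence, and at half sight the guesser gains little over always naming IFN. Most certain entries are also the majority arm. All of this stands, and it limits the size of the point.

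Four stronger readings are tempting, and the protocol does not support them.

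- *About 6 of 60 allocations will be foreseen.* That is an upper bound, needing every earlier allocation in the stratum, in order, from both units.
- *The units pool allocations through the Steering Committee.* The protocol says "The Steering committee will hold at least one meeting a week on teleconference", but the listed topics do not include patient-level allocations, and members need not be enrolling staff. There are other routes: USCAR takes over follow-up of discharged hospital patients (Section 8.3), and both units request drug from the Spallanzani pharmacy on a form naming the unit (Appendix 6). These make some leakage possible; they do not establish that ordered sequences are shared.
- *The 36 hours let staff wait for the preferred arm.* This is a maximum. By then the patient has consented and holds a permanent number, so a later loss leaves a trace. Steering before consent remains possible and does not depend on this interval.
- *No analysis could remove the bias.* Section 10 adjusts for age, gender and co-morbidities, and also considers baseline NEWS2 and recruitment setting. These would remove the measured part of any selection, but not unmeasured frailty.

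**Conclusion.** The point holds as a disclosure weakness. Following the protocol as written gives enrolling staff what they need to deduce some allocations. The gain is at most about 10% certain and 75% guessed right, about 4% and 70% to 71% at three-quarters sight, and about 1% and 68% at half sight, the likely case if the units enrol equally. These figures rest on equal block-length probabilities, 30 patients per stratum and the assumed visibility. No bias in the treatment effect was computed, and nothing in the protocol suggests that steering is intended. Severity is minor to moderate: modest in size, but avoidable in a small open-label trial with 20 controls. It is not a matter for the statistical analysis plan, because the protocol itself makes the disclosure.

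**What to change.** - In Section 9.1, replace the block lengths with a statement that permuted blocks of varying length are used and are not disclosed to enrolling staff.
- Hold the lengths in a restricted randomisation document kept by ISS and the CRO.
- Deleting the sentence is not enough, since 3 and 6 are already known. Generate the list, or its unused remainder, with different multiples of 3, for example 6, 9 and 12. The set finally used should appear in no circulated document. Even if those example lengths were learned, full sight would give about 2% certain and 72% right.

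**Cost.** One sentence, a new list, and a protocol amendment with ethics and authority approval if Section 13.2 is taken to apply. No extra patients, and no change to endpoint or analysis.

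The final split may drift a little further from 40:20. Within an unfinished block of length L, the control count can depart from one third by at most L/3 − L/9 = 2L/9, so by 4L/9 over two strata. That is 2.7 with blocks up to 6 (at most 2 patients) and 5.3 with blocks up to 12 (at most 5). In 20,000 simulated trials with lengths 6, 9 and 12, 99.6% ended with 18 to 22 controls.

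Power, with the pooled standard error for the test and the unpooled one for the alternative, is Φ[(0.35 − 1.96 × 0.1211)/0.1253] = 81.6% at 20:40 and Φ[(0.35 − 1.96 × 0.1228)/0.1301] = 80.0% at 18:42. The loss is small.

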### 9.2 Blinding

This is an open-label study. After the randomization, patient will be notified whether will receive or not the experimental drug.

[figure not shown]

### 9.3 Electronic case report form

Patients' data will be recorded in an *ad hoc* online database. The Electronic case report form will be provided by a Clinical Research Organization and implemented according to the study design. An example of the information to be recorded in the e-CRF is provided as Appendix 4.

### 9.4. Safety Criteria Evaluation

#### 9.4.1 Safety profile

Subjects participating in this trial who received at least one dose of the trial medication are considered to be included in the safety population (full analysis population). Safety population not include subjects who drop out prior to receiving any treatment. Data on safety profile, nature, incidence and severity of adverse events (AEs) and serious adverse events (SAEs) will be collected as detailed in both this section of the protocol and in the AE/SAE section of the CRF. Any reason for drug interruption, reduction and discontinuation will be collected. Toxicities will be graded using NCI Common Terminology Criteria for adverse Events (CTCAE) version 5. The investigator is responsible for detecting, documenting and reporting AEs and SAEs, according to the criteria defined in this protocol.

The safety profile of experimental drug (i.e., IFN- $\beta$ 1a, Rebif®) has been well established. Below are the very common and common adverse reactions as reported in the Summary of Product Characteristic 2010:

| Very common ( $\geq 1/10$ )                                                          | Common ( $\geq 1/100$ to $< 1/10$ )                             |
|--------------------------------------------------------------------------------------|-----------------------------------------------------------------|
| Neutropenia, lymphopenia, leukopenia, thrombocytopenia, anaemia                      | Diarrhoea, vomiting, nausea                                     |
| Asymptomatic transaminase increase                                                   | Severe elevations in transaminases                              |
| Headache                                                                             | Pruritus, rash, erythematous rash, maculopapular rash, alopecia |
| Injection site inflammation, injection site reaction, influenza-like symptoms | Myalgia, arthralgia                                             |
|                                                                                      | Depression, insomnia                                            |
|                                                                                      | Injection site pain, fatigue, rigors, fever                     |

[figure not shown]

## 9.4.2 Adverse events (AE) and serious adverse events (SAE)

### 9.4.2.1 Definition of an AE

An AE is defined as any untoward medical occurrence in a patient, temporarily associated with the use of a medicinal product, whether or not it is considered related to the medicinal product. An AE can therefore be any unfavorable and unintended sign (including an abnormal laboratory finding), symptom, or disease (new or exacerbated) temporarily associated with the use of a medicinal product. Examples of an AE include:

- Significant or unexpected worsening or exacerbation of the condition/indication under study.
- Exacerbation of a chronic or intermittent pre-existing condition including either an increase in frequency and/or intensity of the condition.
- New conditions detected or diagnosed after investigational product administration even though it may have been present prior to the start of the study.
- Signs, symptoms, or the clinical sequelae of a suspected interaction.
- Signs, symptoms, or the clinical sequelae of a suspected overdose of either investigational product or a concurrent medication (overdose per se should not be reported as an AE/SAE).

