### 5.1.1 Primary endpoint and outcome

Primary endpoint of the study is the proportion of patients experiencing a disease progression, during at least 5 days, according to the National Early Warning Score (**NEWS2**). The **NEWS2** score is a standardized approach aimed at promptly detecting signs of clinical deterioration in acutely ill patients and establishing the potential need for higher level of care. It is based on the evaluation of vital signs including respiratory rate, oxygen saturation, temperature, blood pressure, pulse/heart rate, AVPU response. The resulting observations, compared to a normal range, are combined in a single composite “alarm” score. Any other clinical sign clearly indicating a disease worsening will be considered as disease progression.

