## 5.2 Secondary Objectives and Endpoints

The following table 1 contains the secondary objectives and endpoint of the study

| Objective                                                                                                                                                  | Endpoint                                                                                                           |
|------------------------------------------------------------------------------------------------------------------------------------------------------------|--------------------------------------------------------------------------------------------------------------------|
| 1) To assess the reduction in ICU admission in patients treated with IFN versus control group within 28 days of randomization                              | ICU-free days at 28 days (Day 1 through Day 28)                                                                    |
| 2) To assess the reduction in number of deaths in IFN compared to control group (day 28)                                                                   | All-cause mortality (Day 1 through Day 28)                                                                         |
| 3) To evaluate the increase in proportion of participants returning to negative SARS-CoV 2 RT-PCR in IFN-treated versus control group at Day 14 and Day 28 | Negative SARS-CoV 2 RT-PCR at day 14 post-randomization
Negative SARS-CoV 2 RT-PCR at day 28 post-randomization |

|                                                                                                                    |                                                                                      |
|--------------------------------------------------------------------------------------------------------------------|--------------------------------------------------------------------------------------|
| 4) To assess the increase in SARS-CoV 2-Specific Binding Antibody Titers in IFN compared to control group (day 28) | Change from Baseline in SARS-CoV 2-Specific Binding Antibody Titers at day 14 and 28 |
| 5) To assess the safety of IFN-treated patients versus control group                                               | Incidence of adverse events                                                          |

For secondary endpoints, more detailed descriptions follow:

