- 1) ICU-free days at 28 days will be calculated as the number of days a patient is not in an ICU. Time Frame will be: Admission (day 0) to 28 days after admission (day 28). In case of death, it will be counted as 0 day;
- 2) All-cause mortality will be: total number of death events occurring within day 0 and day 28;
- 3) Negative SARS-CoV 2 RT-PCR is defined as an undetectable presence of SARS-CoV 2 genes, as determined by PCR on an adequate sampling of upper respiratory tract.
- 4) Change from Baseline in SARS-CoV 2-Specific Binding Antibody Titers is defined as the difference in anti-SARS-CoV 2-specific antibody levels measured at day 28 versus day 0;
- 5) Details on safety event are described in paragraph 9.4

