#### 5.4 Statistical hypothesis

The trial power has been calculated by the ISS group. The study was powered to independently assess a potential benefit of IFN- $\beta$ 1a compared with control arm (no specific antiviral treatment besides standard of care) on rate of progression of NEWS2 score lasting more than 5 days.

Sample size was calculated according to the primary endpoint of the study. In particular, the sample size calculation is based on the assumptions of an at least 35% difference in the percentage of patients undergoing disease progression between IFN- $\beta$ 1a and control arm. A sample size of 60 patients total (40 in the IFN- $\beta$ 1a-treated arm and 20 in the control arm, according to a 2:1 randomization ratio) will be needed to provide 80% power at significance level of 5% to detect the difference of patients undergoing disease progression between a group 1 proportion of 0.15 (IFN- $\beta$ 1a + standard of care) and a group 2 proportion of 0.50 (standard of care).

[figure not shown]

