### 9.4.2.2 Definition of a Serious Adverse Event

A serious adverse event (SAE) is defined as any untoward medical occurrence that, at any dose:

1. Results in death
2. Is life-threatening
3. Requires hospitalization or prolongation of existing hospitalization
4. Results in disability/incapacity
5. Is a congenital anomaly/birth defect
6. Is otherwise considered as medically important.

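### The compared AE incidence includes COVID-19 worsening, which is also the primary efficacy event, so an overall AE comparison partly restates efficacy and can mask IFN toxicity

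*Protocol*

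**What the plan says.** In the table of section 5.2, the fifth secondary objective is "To assess the safety of IFN-treated patients versus control group", and its endpoint is the incidence of AEs. The notes under the table add: "Details on safety event are described in paragraph 9.4".

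Section 9.4.2.1 defines an AE as an untoward occurrence "temporarily associated with the use of a medicinal product, whether or not it is considered related to the medicinal product". Its first example is "Significant or unexpected worsening or exacerbation of the condition/indication under study". Under section 9.4.2.2 an event that leads to death is an SAE, as is one that meets "Requires hospitalization or prolongation of existing hospitalization". Section 9.4.2.3 requires every AE in the study to be recorded, and Appendix 2 schedules this daily in both arms.

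The primary endpoint (section 5.1.1) is NEWS2 progression of a set duration, widened by this sentence: "Any other clinical sign clearly indicating a disease worsening will be considered as disease progression". Section 10 counts death as a primary event and compares discrete safety endpoints by chi-squared test. Section 5.4 assumes "an at least 35% difference in the percentage of patients undergoing disease progression", namely 50% in controls and 15% on IFN.

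No section separates progression events from the AE incidence that is compared.

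**The concern.** One clinical event can enter both the efficacy comparison and the safety comparison. A treated patient spared progression is also spared an AE, and perhaps an SAE. If IFN works as planned, overall AE incidence moves in its favour without any gain in tolerability, and that movement can offset a real excess of drug reactions. If IFN does not affect progression, events common to both arms dilute the excess.

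Section 1.4 says the treatment could be extended to home and care-home patients once efficacy and safety are shown. For elderly patients with mild disease, a statement that AEs were no more frequent than in controls carries weight. It should not be largely a second reading of the primary endpoint.

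**Working it through.** **Inputs from the protocol.** Progression is q = 0.50 in controls and 0.15 on IFN (5.4). There are 20 controls and 40 IFN patients (5.4, 9.1), with a two-sided test at 0.05 (10).

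**The plan's own figure.** Uncorrected Fleiss formula, 2:1, with pooled proportion (0.50 + 2×0.15)/3 = 0.267:

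n(control) = [1.96·√(1.5×0.267×0.733) + 0.842·√(0.50×0.50 + 0.15×0.85/2)]² / 0.35² = (1.062 + 0.471)²/0.1225 = 19.2, so 20 controls and 40 IFN. The stated 60 reproduces.

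**Assumed input.** The protocol gives no rate of AEs other than progression. Call it c in controls and t on IFN, and vary it. The any-AE proportion is 1 − (1 − q)(1 − t) if other AEs are independent of progression, and max(q, t) if they overlap in the same patients as far as possible. Chances of significance come from exact enumeration of the uncorrected chi-squared test at 40 versus 20.

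**1. Upper bound.** If every progression is logged as an AE and there are no other AEs: 0.15 − 0.50 = −35 points.

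**2. IFN adds no other AEs (t = c).** IFN minus control, with the chance that IFN looks significantly safer in the independent case:

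| c | Control | IFN | Difference | Chance | Difference, full overlap of patients |
|---|---|---|---|---|---|
| 0.2 | 0.600 | 0.320 | −28.0 | 56% | −30 |
| 0.3 | 0.650 | 0.405 | −24.5 | 45% | −20 |
| 0.4 | 0.700 | 0.490 | −21.0 | 35% | −10 |
| 0.5 | 0.750 | 0.575 | −17.5 | 27% | 0 |
| 0.6 | 0.800 | 0.660 | −14.0 | 20% | 0 |
| 0.7 | 0.850 | 0.745 | −10.5 | 13% | 0 |
| 0.8 | 0.900 | 0.830 | −7.0 | 8% | 0 |
| 0.9 | 0.950 | 0.915 | −3.5 | 2% | 0 |

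A nominal two-sided test would give about 2.5% in that direction.

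**3. IFN truly adds other AEs, t = 0.50 against c = 0.30 (+20 points).** Chance of a significant excess on IFN:

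| What is counted | Control | IFN | Difference | Chance |
|---|---|---|---|---|
| Progression left out | 0.300 | 0.500 | +20 | 32% |
| Progression counted, 15% v 50% | 0.650 | 0.575 | −7.5 | 0.6% |
| Only half of progressions logged, 7.5% v 25% | 0.475 | 0.5375 | +6.25 | 7% |
| 35% of IFN patients progress v 50% | 0.650 | 0.675 | +2.5 | 4% |
| No effect on progression, 50% v 50% | 0.650 | 0.750 | +10 | 13% |

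With full overlap of patients at the planned effect, both arms show 0.50 and the difference is 0.

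**4. A second set of assumptions.** Take 10% background AEs in both arms and 30% extra toxicity on IFN. Without progression this is 10% versus 37%, with a 65% chance of detection. With progression it is 55.0% versus 46.5%, and 0.5%.

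**5. Precision.** The 95% half-width, 1.96·√[p(1 − p)(1/40 + 1/20)], is 24.6 points at p = 0.3 and 26.8 at p = 0.5. The comparison is imprecise in any case.

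**The case against.** The strongest reply is that the protocol never says the compared statistic is patients with at least one AE of any kind. Section 9.4.1 speaks of nature, incidence and severity. Section 10 names tests for several types of variable. AEs are recorded one by one, graded and assessed for causality. Appendix 4 Table 4 lists the known Rebif reactions. A split by type is therefore possible, and the statistical analysis plan, which is not at hand, may contain one. The individual stopping rule in section 8.5 uses drug-related events of grade 3 or more, so it does not depend on the pooled count.

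Much of this stands. The toxicity data are not lost, and term-level counts that COVID-19 does not cause are unaffected. But the protocol fixes the endpoint, the AE definition and the test without a split, and an analysis that follows it literally inherits the overlap. The causality assessment (9.4.2.4.2) does not supply the split: it asks about the study product, which controls never receive, and it is made open-label.

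Four stronger readings are tempting, and the documents do not support them:

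- A reader might infer that the AE definition is wrong. Counting worsening of the studied disease is an acceptable recording rule.
- A reader might infer that IFN starts with a 35-point advantage. The definition covers only worsening that is significant or unexpected, so 35 points needs complete overlap and no other AEs.
- A reader might infer that the distortion is always large. Daily recording for 28 days in patients aged 65 or older, with abnormal laboratory findings included, makes high other-AE rates plausible, and the shift is then small.
- A reader might infer that a toxicity signal would be reversed. That needs a substantial effect on progression; with none, the excess is only diluted.

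**Conclusion.** The point holds as a directional weakness in the compared safety endpoint, not as an error in AE recording. At the planned 50% versus 15%, overall any-AE incidence shifts towards IFN by at most 35 points. The shift is 14 to 28 points if other AEs affect 20-60% of patients independently of progression. It is about 10 points or less if they affect 70% or more, or if they affect 40% or more and fall in the same patients as progression. It is zero in that overlapping case from 50% upwards.

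Under assumed true other-AE rates of 50% versus 30%, the chance of detecting the excess drops from 32% to 0.6% at the planned effect, 7% if half of progressions are logged, and 13% if IFN has no effect on progression. All other-AE rates are assumptions. The safety comparison is imprecise at 40 versus 20 whatever is done, but imprecision has no preferred direction, whereas this shift favours IFN whenever IFN reduces progression. It is a cheap improvement and worth making before the data are seen, because a split chosen afterwards in an open-label trial is open to challenge.

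**What to change.** Leave AE and SAE recording and expedited reporting unchanged. In section 5.2 (fifth row) and section 10, pre-specify that AE incidence is compared between arms from T1 to T28 in two ways:

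1. all AEs;
2. all AEs except those that are the patient's recorded primary-endpoint event, meaning the progression or death counted in the primary analysis.

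State that a listed Rebif reaction (Appendix 4, Table 4) always counts, also during a progression episode. State that any claim of comparable or better safety must not rest on the all-AE count alone.

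Do not remove dyspnoea, hypoxia or pneumonia by term, and do not require deaths to be attributed to COVID-19. The first would take possible drug harm out of the comparison, and the second needs open-label judgement.

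The cost is wording in two sections and one extra tabulation from data already collected. The downside is that worsening or death caused by IFN leaves the second count. It stays in the all-AE count and in the primary, ICU-free-days and mortality endpoints. Symptoms common to COVID-19 and Rebif, such as fever, headache and myalgia, still count in both arms, so some dilution remains.
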